#### Audiology outcomes

Differences in hearing level at 12 months will be assessed using a simple linear regression. The absolute mean difference and the 95% confidence interval between the two interventions will be reported. The baseline hearing level will be adjusted in an analysis of covariance (ANCOVA). Further, the stratification factors and the other intervention will be included as explanatory variables to assess their effects on the hearing outcome.

#### Other outcomes

Complications, defined as proportions of children that develop illness requiring additional medication and proportions of children with any illness requiring cessation of prescribed treatment will be compared between treatments using a Chi-square test.

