
## Methods

### Study design

This is a parallel group, 2 × 2 factorial design, randomised (allocation concealed), assessor blinded, controlled clinical trial. This RCT was conducted in the Northern Territory (NT) and aimed to compare current standard treatment (twice daily dry mopping, ciprofloxacin drops and weekly clinic review) with two adjunctive therapies. Each child was randomised to receive standard treatment plus one of two topical treatments (povidone-iodine ear wash or no ear wash) and one of two oral medication treatments (cotrimoxazole or placebo) for 16 weeks.

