### Randomisation

Eligible children whose parent or guardian provided signed informed consent were randomised to one of the four treatment options according to a computer-generated sequence. This was obtained by a phone call (interactive voice response system) to the NHMRC Clinical Trial Centre (CTC). Children were stratified according to community and age (<4y, 4-10y, >10y) using a minimisation procedure**.** The allocation sequence was concealed from all investigators throughout the study. Study staff were blinded to the oral component of the treatment at randomisation and follow-up assessments. However, it was not possible to blind the topical treatment groups. All laboratory staff are blinded. The randomisation of an individual participant would only be unblinded in emergency situations where the chief investigator and study’s medical monitor feels the emergency cannot be adequately addressed without knowing which treatment was delivered.

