### Intervention

Intervention 1: The active oral medication used for this trial is cotrimoxazole suspension (or tablet for children over 12 years of age). A non-active formulation of the exact colour, taste and appearance as the intervention was used as the placebo. Cotrimoxazole suspension was given as 4 mg/kg per dose (of trimethoprim component) twice a day orally for 16 weeks. The placebo was administered in an identical manner.

Intervention 2: The topical treatment was aqueous povidone-iodine 10%, diluted in clean, room temperature water (1:20). Each discharging ear was syringed twice daily using a 20 ml syringe for up to 16 weeks or until the ear was dry for 14 days (confirmed on two clinical examinations 1 week apart by study or clinic staff). Treatment was recommenced if discharge becomes present again.

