### Outcome measures

The primary outcome measure was the proportion of children with clinical failure after 16 weeks (4 months) of treatment. Clinical failure was determined by clinical examination for the presence of any ear discharge. Additional secondary outcome measures at 4 months and 12 months included: i) hearing level, determined by audiometry (performed by trained audiologists) and summarised as the pure tone 4 frequency average hearing level at 500, 1000, 2000 and 4000 Hz in the better and worse hearing ears; ii) failure to improve (determined by perforation size and amount of discharge); iii) change in perforation size and amount of discharge (determined by comparison of standardised assessment at baseline with end of study); iv) time to cessation of discharge (determined by review of health records); v) adherence to recommended management including attendance for specialist review (determined by review of health records); vi) presence of recognised bacterial pathogens in nose and ear discharge (determined by standard microbiological culture and antimicrobial sensitivity methods); vii) complications (defined as development of a related illness requiring additional medical treatment); and viii) side effects (defined as development of illness requiring cessation of prescribed treatments). Additional secondary outcomes at 4 months and 12 months from randomisation included the proportion of children with any carriage of pneumococci and any carriage of vaccine or non- vaccine serotype pneumococci and any carriage of NTHi. All children were followed up for any adverse events (AE) and serious adverse events (SAE) by reviewing the child’s clinic and hospital records and asking the parents about any side effects of the treatments between and at visits. We documented any contact the family or child had during the study with the clinic or hospital, including all relevant investigations and treatments. Regular, scheduled home visits, phone calls, SMS texts and social media contact with the families were made and recorded by study nurses or community researchers to support and promote participant retention; and monitor adherence.

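### For wash v no wash, the side-effect outcome counts stopping any prescribed treatment, and the wash group has one more treatment to stop, so an excess does not by itself show side effects of the wash

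*Protocol article*

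**What the plan says.** Outcome measures lists, among the secondary outcomes, "side effects (defined as development of illness requiring cessation of prescribed treatments". Other outcomes gives the analysis: "proportions of children with any illness requiring cessation of prescribed treatment will be compared between treatments using a Chi-square test". Neither section names the treatment that must be stopped or limits the count to treatments that both groups receive.

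Study design sets out what each child receives. Everyone has standard care, described as "twice daily dry mopping, ciprofloxacin drops and weekly clinic review". On top of that, each child is allocated "one of two topical treatments (povidone-iodine ear wash or no ear wash) and one of two oral medication treatments (cotrimoxazole or placebo". The comparator for the wash is therefore the absence of a wash, with no sham procedure. Randomisation adds that "it was not possible to blind the topical treatment groups". For the oral factor the position differs. Intervention describes a placebo matched in colour, taste and appearance, and says: "The placebo was administered in an identical manner".

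**The concern.** An event under this definition needs two things: an illness, and a treatment that is stopped because of it. In the wash group there are three products to stop (ciprofloxacin drops, oral product, wash). In the no-wash group there are two (drops, oral product). An illness that leads only to the wash being stopped is an event in one group, and the same illness cannot be an event in the other. Because the topical groups are open, whoever decides to stop also knows that there is a wash to stop.

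Equal illness in the two groups therefore does not guarantee equal event proportions. A significant excess with the wash could be reported as side effects of the wash although part of it reflects only the extra item in the regimen. The Discussion expects the results to guide treatment of Indigenous children with CSOM, so the label put on this comparison matters.

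The cotrimoxazole v placebo comparison does not have this problem, because both oral groups have an oral product that can be stopped.

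**Working it through.** **Inputs from the protocol article.** 280 children are planned, and Statistical methods compares groups of 140 on each factor (280 / 2 = 140). The test is Chi-square, two-sided at 5% (Other outcomes, Missing data). Stoppable products number three with the wash and two without (Study design). Dry mopping is common to both groups, so counting it would still leave a difference of one. The article gives no figure for this outcome, so there is nothing of its own to reproduce.

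**Assumptions.** Each product is stopped for illness in a proportion c of children, with c = 2%, 3% or 5%, and the wash causes no illness. These are illustrations, not figures from the documents.

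**Step 1: no-wash group.** P(any stop) = 1 − (1 − c)².
- c = 2%: 1 − 0.98² = 4.0%
- c = 3%: 1 − 0.97² = 5.9%
- c = 5%: 1 − 0.95² = 9.8%

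**Step 2: wash group, with wash stops independent of other stops.** P(any stop) = 1 − (1 − c)³.
- c = 2%: 1 − 0.98³ = 5.9%
- c = 3%: 1 − 0.97³ = 8.7%
- c = 5%: 1 − 0.95³ = 14.3%

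The ratio of wash to no wash is between 1.46 and 1.49.

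**Step 3: overlap.** If a share o of wash stops occurs in children who also stop another product, only c(1 − o) is added to the no-wash figure. With o = 50% and c = 5%, the wash group has 9.75% + 2.5% = 12.25% (ratio 1.26). With o = 80% it has 9.75% + 1.0% = 10.75% (ratio 1.10). With o = 100% the groups are equal.

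**Step 4: false rejection.** Exact binomial enumeration of the uncorrected Chi-square test, 140 per group:

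| Wash stops | c = 2% | c = 3% | c = 5% |
|---|---|---|---|
| Independent of other stops | 11.0% | 13.9% | 21.1% |
| 50% coincide with another stop | 6.5% | 7.4% | 10.1% |
| 80% coincide | about 5% | 5.2% | 5.7% |
| 100% coincide (equal risk) | 4.6% | 4.8% | 4.8% |

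If 50% overlap is instead taken to halve the excess found under independence, the second row becomes 6.4%, 7.1% and 9.1%. In the independent case, nearly all rejections are in the direction of the wash looking worse. With 126 per group (140 less the 10% loss in Sample size), that row is 10.1%, 13.4% and 19.3%.

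**Step 5: a second model.** Let the same 20% to 40% of children in each group fall ill, and let each product be stopped independently with probability s given illness. For s = 0.1 to 0.5 and 126 per group, the ratio runs from 1.43 down to 1.17, and a significant result against the wash occurs in 7.5% to 19.4% of trials (about 2.5% expected). At s = 1 the ratio is 1.00 and the excess disappears.

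**Step 6: after the change.** If only cessation of drops or oral product is counted, both groups have 4.0%, 5.9% or 9.8% under these assumptions. The test then rejects in 4.6% to 4.8% of trials.

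**The case against.** The strongest reply is that this is an add-on trial. Illness leading to cessation of any part of the regimen, standard care plus wash against standard care, is a legitimate measure of tolerability, and Other outcomes does not claim that the test isolates what the wash causes. That stands as a reason to keep the comparison. It does not stand as a reason to call the result side effects, which is the name Outcome measures gives it.

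Second, the size depends on the overlap assumption. An ear illness that stops the wash may well stop drops in the same ear, and a systemic illness may stop the oral product too. This stands: at 80% overlap the test is close to its nominal level, so the 11% to 21% range is the independent case and not an estimate for this trial.

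Third, safety of the wash does not rest on this test. Other outcomes also compares illness needing additional medication, Safety monitoring describes day-three and continuing checks with independent board review, and Outcome measures follows adverse and serious adverse events in all children. This lowers the stakes but does not change what the cessation comparison measures.

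Fourth, a fuller protocol or analysis plan may define cessation by treatment. That is possible. The point here rests on the definition and test that the article itself fixes.

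**Conclusion.** The point holds in a limited form. For wash v no wash, the stated event can be reached by one more route in the wash group, so a Chi-square excess may partly reflect having a wash to stop and is not sufficient evidence of wash side effects. The size cannot be fixed from the documents. It ranges from none, if every illness that stops the wash also stops something else, to false rejection of about 11% to 21% under independence with c between 2% and 5%. The oral comparison, the primary outcome and the sample size are untouched. It is a minor point on a secondary safety outcome.

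A reader might infer three stronger things that the documents do not support.
- That the test will produce a false signal against the wash. The definition only allows it, and no cessation rates are given.
- That time at risk differs because the wash runs "for up to 16 weeks or until the ear was dry for 14 days", so that early responders can no longer stop it for illness. Intervention goes on to say that treatment restarts if discharge returns, and the Abstract says that the drops also end on resolution.
- That counting the outcome at 12 months is an error because trial treatment ends by week 16. Outcome measures uses one umbrella phrase for all its secondary outcomes, Other outcomes sets no timepoint, and the treatments counted are not limited to trial products.

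**What to change.** - Tabulate cessation for illness by treatment stopped (drops, oral product, wash) in each group.
- Compare wash v no wash on cessation of the treatments that both groups take, namely drops and oral product.
- Report cessation of the wash for illness as a percentage with a 95% CI, within the wash group only.
- Keep the any-cessation comparison, labelled as regimen tolerability and not as side effects of the wash.
- Read harm of the wash from these together with the complications outcome and the AE/SAE follow-up already planned.

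The cost is a change of analysis wording and one extra table, drawn from clinic and hospital records that are reviewed anyway. Trial status says that data cleaning has only commenced, so the wording can still be settled before analysis. There is a small downside: the shared-treatment comparison has fewer events, and it cannot on its own show illness that stops only the wash, which is the most direct sign of wash intolerance. It therefore should not stand alone.

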### Sample size

We estimate that at least 70% of children receiving current standard therapy for CSOM will (unfortunately) not be cured after 16 weeks of treatment. [8] The target enrolment was 280 participants. This study would have 90% power to detect an improved outcome in an additional 20% of children for each intervention (at the 5% significance level), assuming 10% loss to follow up or withdrawal.

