#### Primary clinical outcomes

The primary endpoint is the proportion of children with clinical failure of CSOM after 16 weeks (4 months) of treatment. A binomial regression with logarithmic and identity link will be used to estimate the main effects of the two interventions. Therefore, the relative risk and the risk difference, respectively, with their 95% confidence interval will be reported for the crude and adjusted estimates. The adjustment set will comprise of the stratification factors (age group and community) and the other intervention.

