#### Missing data

The number of participants with primary endpoint and other data available at required timepoints, will be reported. No data imputation for missing data will be carried out. Where reasonable, complete case analysis will apply. All analysis will be two-tailed and statistical significance will be set at *p* < 0.05, using Stata 15.1 (StataCorp, College Station, TX, USA).

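### Complications and illness-related treatment cessation get a bare Chi-square test, so the amount of harm still compatible with the data is not planned to be shown (minor; cheap to improve)

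*Protocol article*

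**What the plan says.** The Other outcomes section of the protocol article covers two proportions. One is complications, meaning illness that needs extra medication. The other is "proportions of children with any illness requiring cessation of prescribed treatment". Both "will be compared between treatments using a Chi-square test", and the section names no effect measure, confidence interval or adjustment. The second proportion matches a listed secondary outcome in Outcome measures: "side effects (defined as development of illness requiring cessation of prescribed treatments". Complications are listed there too, so both will be formally reported.

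The Missing data section adds a general rule: "All analysis will be two-tailed and statistical significance will be set at" p < 0.05.

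The neighbouring outcomes are treated differently:
- Primary clinical outcomes: "the relative risk and the risk difference, respectively, with their 95% confidence interval will be reported", crude and adjusted for age group, community and the other intervention.
- Secondary clinical outcomes and Carriage outcomes: the primary method, by reference.
- Audiology outcomes: a mean difference with a 95% confidence interval.

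The Statistical methods section sets the comparisons in general terms: wash against no wash and cotrimoxazole against placebo, each with 140 children per group.

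**The concern.** For these two outcomes the stated inferential output is a significance verdict. The trial was sized for a large difference in a common outcome, so a non-significant result on adverse outcomes would be unsurprising even if one of the added treatments did cause harm. What a reader needs is the range of excess risk that the data have not ruled out, for each added treatment separately. The article plans that summary for its other binary outcomes but not for these.

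This is more than a detail left to a fuller plan. The article does choose an analysis here, and the one it chooses is less informative than the one it uses elsewhere.

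**Working it through.** **1. The plan's own figure.** Sample size states: "The target enrolment was 280 participants", with "90% power to detect an improved outcome in an additional 20% of children for each intervention (at the 5% significance level", and assumes that "at least 70% of children receiving current standard therapy for CSOM will (unfortunately) not be cured after 16 weeks of treatment". Inputs: failure 70% against 50%, two-sided 5%, 90% power, 10% loss, each factor compared at its margin.

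- n per margin = [1.96 × √(2 × 0.6 × 0.4) + 1.2816 × √(0.7 × 0.3 + 0.5 × 0.5)]² / 0.20² = 124.
- Allowing for loss: 124 / 0.9 = 138 per margin, or 276 in total, against 280 stated.

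The stated size reproduces and is not in dispute. It is a size for a 20-point difference in a common outcome.

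**2. What the Chi-square test reports.** The article gives no event rate for complications or cessations, so these counts are assumed: 8 events among 140 children on an intervention and 3 among 140 on its control. The margin size of 140 is from Statistical methods.

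- Proportions: 8/140 = 5.71% and 3/140 = 2.14%. Pooled: 11/280 = 3.93%.
- X² = (0.0571 − 0.0214)² / [0.0393 × 0.9607 × 2/140] = 2.37 on 1 df, p = 0.124. Fisher's exact p = 0.217.

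Under the planned rule the result is not significant, and the named analysis stops there.

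**3. What an estimate with an interval reports for the same counts.**

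- Risk difference: 5.71 − 2.14 = +3.57 points.
- Wilson limits: 2.92% to 10.87% for 8/140, and 0.73% to 6.11% for 3/140.
- Newcombe lower limit: 3.57 − √[(5.71 − 2.92)² + (6.11 − 2.14)²] = −1.3 points.
- Newcombe upper limit: 3.57 + √[(10.87 − 5.71)² + (2.14 − 0.73)²] = +8.9 points.
- Relative risk: 8/3 = 2.7, score 95% CI 0.78 to 9.15.

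**4. Does this depend on the chosen counts?** Two other assumed pairs, at 140 per margin:

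| Events | Chi-square p | Risk difference, points (95% CI) | Relative risk (95% CI) |
|---|---|---|---|
| 6 v 2 | 0.15 | +2.9 (−1.4 to 7.7) | 3.0 (0.70 to 12.9) |
| 8 v 3 | 0.12 | +3.6 (−1.3 to 8.9) | 2.7 (0.78 to 9.2) |
| 12 v 6 | 0.14 | +4.3 (−1.7 to 10.5) | 2.0 (0.80 to 5.0) |

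The three p-values are almost the same and support the same verdict. The intervals differ in what they leave open: upper limits of 7.7, 8.9 and 10.5 points, and relative risks up to about 13, 9 and 5. The p-value carries none of that information.

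**The case against.** Several stronger readings are tempting, and the document does not support them.

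- **That the Chi-square test is underpowered for harm and should be replaced for that reason.** Low power comes from the number of children, not from the choice of test. An interval from the same data would exclude zero about as often. The remedy displays the uncertainty and does not reduce it.
- **That the test is a four-arm, 3-df comparison with very small expected counts.** Other outcomes says only that treatments are compared, but Statistical methods has already set the comparisons at the two margins. The four-arm reading is the less natural one, and nothing should rest on it.
- **That the test is invalid with few events.** By exact enumeration at 140 per margin and an assumed 2% rate in both groups, the uncorrected marginal test rejects 4.5% of the time, so it keeps its nominal level there.
- **That the events will be sparse.** This is an assumption. Illness needing extra medication could be common: the Background reports that 75% of children who sought care in the team's most recent study were prescribed amoxycillin.
- **That leaving out the other intervention distorts the result.** With near-equal allocation in a 2 × 2 factorial it causes little bias. With few events an adjusted binomial model may not converge, so an unadjusted comparison is defensible.
- **That the investigators will take p > 0.05 as proof of safety.** The article does not say so. Safety monitoring gives review of all adverse events to an independent board, and stopping rules exist in the full protocol.

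It is also fair to say that a reader given the proportions and group sizes could work out the interval, and that a fuller plan may add estimates. Neither fully answers the point. The article fixes a test as the analysis for these outcomes while fixing estimates for the others, and the board's oversight during the trial does not replace the published comparison.

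**Conclusion.** The point holds in a limited form. For complications and illness-related cessation, the article specifies a significance test where it specifies an effect estimate for every other outcome with a named comparison. With 140 per margin and counts of the assumed order, a non-significant result can coexist with an excess risk of up to about 9 points or a ninefold relative risk, and the stated analysis would not show it. The counts are illustrative, because the document gives no event rates. The conclusion that a p-value omits the size of harm does not depend on them.

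Severity is minor. These are secondary outcomes, the primary analysis and sample size are unaffected, and the change is a cheap improvement in reporting.

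**What to change.** In Other outcomes, replace the Chi-square test as the stated analysis. For each intervention at its margin (wash against no wash; cotrimoxazole against placebo), report the number of children with the event and the group size, together with the risk difference and relative risk and their 95% confidence intervals. Use score or exact limits when counts are small. Show the four-arm counts descriptively. Treat adjustment for the other intervention as optional, where the model converges. State that no conclusion of safety will be drawn from p > 0.05.

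The cost is a few words and a few lines of code, on data already being collected. Trial status describes data cleaning as only begun, so at that stage the change could still precede the analysis. The only downside is that wide intervals will be shown openly.
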